### Intervention

The eCBT-I comprises six guided weekly sessions provided online, combined with two face-to-face sessions of 60 min and a smartphone diary-app for daily reporting of sleep times and subjective sleep quality. Each session is structured around one topic and contains specific information, assignments and testimonials of two patients with insomnia after brain injury to illustrate sleep problems and homework assignments. All participants will receive online personal feedback after each session and will be encouraged to practice daily with the provided exercises, downloadable within the eHealth intervention on a daily basis. Participants can start with the next session after they have read their personal feedback. They can contact their therapist at any time by means of the integrated email function. Participants will be encouraged to complete the diary every day by their therapist.

The eCBT-I is based on well-established CBT-I components and includes behavioral and cognitive techniques. These techniques contain sleep hygiene education, stimulus control, sleep restriction, cognitive restructuring, activation, relaxation, and fatigue and stress management. The eCBT-I has been adjusted to people with acquired brain injury in general, both with respect to content and the way of conveying information. Content adjustments include specific education about the nature and treatment of insomnia after acquired brain injury, testimonials of patients with insomnia following acquired brain injury, and adaptations to cognitive impairments due to brain damage. Information is given in clear and short texts and is visually supported. An option is included to allow for listening to an audio version of the texts. All sessions follow the same structure, with repetition of key points. Specific feedback suggestions for each session will be provided for the therapists.

The length of our eCBT-I protocol of 6 weeks is comparable with eCBT-I protocols in other studies. The CBT-I protocol in other studies examining efficacy in ABI consisted of 4 to 8 weekly sessions [12–17], and 6 weeks for eCBT-I [18]. In a review on the efficacy of eCBTI in the general population, an average length of 5.5 weeks was found, with a range of 2–9 weeks [11].

The eCBT-I will be given by an experienced registered healthcare psychologist, trained in using the eHealth intervention. Adherence will be monitored by checking frequency of registration in the sleep diary app, time spent online, and online assignments done. For a detailed description of the intervention per week, see Table 1.

### Outcomes

#### Sleep outcome measures

The primary outcome measure is the change in insomnia severity measured with the Dutch version of the Insomnia Severity Index (ISI) at posttreatment. The ISI consists of 7 items and uses a 5-point scale to measure to which extent participants experience insomnia. The total score ranges from 0 (no insomnia) to 28 (severe insomnia). A cut-off of 10 is used to indicate clinical levels of insomnia in this study, similar to other studies [20–22]. The Minimally Clinical Improvement Difference (MCID), which indicates the minimal improvement to be clinically significant, is a reduction of six points [23]. The internal consistency is adequate (Cronbach’s alpha = 0.74–0.78). The ISI is selected as it is sensitive to treatment response [22, 24] and used in comparable research worldwide, including the Netherlands [20, 21]. Secondary sleep outcome measures include overall sleep disturbances assessed with the Pittsburgh Sleep Quality Index [25] and the following sleep features derived from the sleep diary app: total sleep time, sleep onset latency, number of nocturnal awakenings, sleep efficiency, and subjective sleep quality.

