### Objectives

The objectives of this study are:
To evaluate the efficacy of eCBT-I in reducing insomnia severity posttreatment and at 6-week follow-up in patients with insomnia following a stroke or TBI, as compared to treatment as usual (TAU)To evaluate the efficacy of the eCBT-I in reducing complaints about fatigue, cognitive functioning, emotional well-being, and societal participation posttreatment and at 6-week follow-up compared to TAUTo explore whether treatment efficacies vary with severity of insomnia, with the severity and type of brain injury, and with the time since brain injury.

Our primary hypothesis is that eCBT-I will reduce insomnia posttreatment more than treatment as usual, compared to baseline. Our secondary hypotheses are that eCBT-I will improve fatigue, cognitive functioning, emotional well-being, and societal participation.

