## Methods

### Study design

The randomized controlled trial (RCT) uses a multicenter, prospective, randomized, open-label, blinded end point study design (PROBE) [19] to compare eCBT-I with TAU. A total of 48 patients will be randomly assigned to the eCBT-I or TAU group. Assessment will be performed at baseline (T1), 1 week after the 6-week intervention period (T2), and after 6-week follow-up (T3). The total duration of participation is 14 weeks. See Fig. 1 for a flowchart.

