### Sample size calculation

Calculation of power and group size in a repeated measures design requires an estimate of the expected intraclass correlation coefficient (ICC, within subject correlation). We therefore resorted to a recent randomized trial of Dekker and colleagues (2020) on the effect of eCBT-I on ISI in people with insomnia. We used this intraclass correlation coefficient as indication of follow-up of ISI assessments across 6 weeks in our study population with acquired brain injury. That study reported an ICC of 0.54 for ISI assessments repeated across 6 weeks in 175 people suffering from insomnia without brain injury [33]. Calculation of power and group size moreover requires an estimate of the expected treatment effect size. Whereas treatment effects of eCBT-I are often reported to be of moderate to large size, we preferred to be somewhat conservative and expect a somewhat smaller than moderate effect in the population of TBI and stroke and therefore used *f* = 0.20. Calculation of the required sample size using G*Power [34] for ANOVA, with two repeated measures and ICC of 0.54, indicated that 48 completers would provide (2 × 24), at a significance of alpha = 0.05, sufficient power (1-beta = 0.80) for a minimal detectable time-by-group interaction effect of *f* = 0.20 (small to moderate).

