### Statistical analyses

Data analysis will be performed with SPSS 23 (IBM; Armonck, USA). Means and standard deviations of the demographic and injury-related variables and the clinical characteristics collected at baseline will be calculated. As normality assumptions may not be met with this small sample size, data distributions and all model assumptions will be checked for all analyses. If model assumptions are not met, data will either be transformed or analyzed using a non-parametric test, as appropriate. For data not normally distributed, median and interquartile range will be reported. Independent *T* tests will be used to check for an imbalance between groups. Nominal variables will be checked with *χ*^2^ tests and ordinal variable with the Mann-Whitney Test. Statistical significance will be set at a *p* value of 0.05. To accommodate likely occasional missing days, the repeated measures obtained by diaries will be analyzed with mixed effect models. The treatment effects will be examined using a repeated-measures ANOVA. In the case of significant baseline imbalance, post hoc analysis of covariance (ANCOVA) will be used on the change scores of the outcome measures with baseline scores as covariates. Intention-to-treat analyses will be conducted and presented as primary results. Additionally, a per-protocol analysis will be performed. Also, we will compare the eCBT-I and TAU group with regard to the percentage of participants who have improved (reduction ≥ 6 points on the ISI) and recovered (ISI < 10). We will use mixed effect regression models to explore whether treatment efficacy, i.e., the time-by-treatment effect, is modified by time since brain injury and by diagnosis (stroke versus TBI).

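### The repeated-measures ANOVA is not tied to the primary T1–T2 change in ISI; a baseline-adjusted T2 comparison should be named as the single primary test

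*Protocol article*

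**What the plan says.** Three parts of the protocol article point to the change from baseline (T1) to posttreatment (T2).

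- Under Sleep outcome measures, the endpoint is defined: "The primary outcome measure is the change in insomnia severity measured with the Dutch version of the Insomnia Severity Index (ISI) at posttreatment".
- Objectives, final paragraph: "Our primary hypothesis is that eCBT-I will reduce insomnia posttreatment more than treatment as usual, compared to baseline".
- Sample size calculation: the 48 completers were obtained "for ANOVA, with two repeated measures and ICC of 0.54", for a time-by-group interaction of f = 0.20 at alpha 0.05 and power 0.80. The two measures are not named as visits.

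Other parts are wider. Study design and Table 3 schedule the ISI at T1, T2 and T3. The first objective is "To evaluate the efficacy of eCBT-I in reducing insomnia severity posttreatment and at 6-week follow-up", with neither time point ranked above the other.

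The Statistical analyses section names the efficacy test in one sentence: "The treatment effects will be examined using a repeated-measures ANOVA". It does not say how many levels time has or which contrast decides the primary hypothesis. Later in the section, in the sentence on effect modification, efficacy is glossed as "treatment efficacy, i.e., the time-by-treatment effect". Baseline-adjusted ANCOVA appears only as a post hoc step if the groups differ significantly at baseline.

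**The concern.** In a study with three ISI visits, one sentence covering all treatment effects can be carried out in two ways. With time at two levels (T1, T2), the interaction has 1 degree of freedom and is the test that was powered. With time at three levels, the interaction has 2 degrees of freedom and asks whether the groups' profiles differ anywhere across the three visits.

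The second version can be significant because of T3 alone, so it would not establish a posttreatment benefit. It can also miss a T2 benefit that fades. The article leaves the choice between the two open.

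There is also a question of efficiency. Under either version, baseline ISI enters only as one of the repeated outcomes. The more precise baseline-adjusted comparison is held back until a significance test on baseline happens to reject.

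**Working it through.** **Inputs from the Sample size calculation.** N = 48 (24 per arm), f = 0.20, ICC ρ = 0.54, m = 2 measures, alpha 0.05, target power 0.80.

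**Assumptions.** Equal correlation of 0.54 between all pairs of visits, equal SD at each visit (set to 1), and complete data. The T3 effects are assumed, because the article gives none.

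**1. The plan's own figure.** For the within-between interaction in G*Power, λ = f²·N·m/(1−ρ), with df (m−1) and (N−2)(m−1).

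- m = 2, N = 48: λ = 0.04 × 48 × 2 / 0.46 = 8.35 on F(1, 46); power 0.807.
- m = 2, N = 46: power 0.790. So 48 is the smallest even total, and the stated figure is reproduced.
- m = 3, N = 48, same f: λ = 0.04 × 48 × 3 / 0.46 = 12.52 on F(2, 92); power 0.886. N = 40 would already give 0.817.

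The stated 48 therefore belongs to a two-level test.

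**2. The planned effect in SD units.** With two groups and two measures, a between-group difference in change of d gives interaction terms of ±d/4. So f = d/4 and d = 4 × 0.20 = 0.80 SD. As a check, the change score has variance 2(1−0.54) = 0.92 and the SE of the difference is √(2 × 0.92/24) = 0.277. Then 0.80/0.277 = 2.89, and 2.89² = 8.35, the same λ. The two-level ANOVA interaction and a t-test on change scores are the same test.

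**3. The three-level interaction.** With group differences d₁, d₂, d₃ at T1, T2, T3, λ = (N/4)·Σ(dⱼ − d̄)²/(1−ρ) on F(2, 92).

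| Differences at T1, T2, T3 (SD) | Σ(dⱼ − d̄)² | λ | Three-level interaction significant | T1–T2 test significant |
|---|---|---|---|---|
| 0, 0, 0.8 | 0.427 | 11.13 | 0.845 | 0.05 |
| 0, 0.8, 0.4 | 0.320 | 8.35 | 0.722 | 0.807 |
| 0, 0.8, 0.6 | 0.347 | 9.04 | 0.758 | 0.807 |
| 0, 0.8, 0.8 | 0.427 | 11.13 | 0.845 | 0.807 |

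Simulation (20,000 trials per pattern) of the first, second and fourth rows gave 0.847, 0.725 and 0.843 for the three-level interaction, and 0.051, 0.811 and 0.804 for the T1–T2 test.

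**4. Baseline-adjusted T2 comparison.** The residual variance is 1 − 0.54² = 0.708, against 0.92 for the change score, a ratio of 0.77. The SE is √(2 × 0.708/24) = 0.243 and 0.80/0.243 = 3.29. On 45 df the power is 0.896. A simulation of 20,000 trials that lets baseline means differ by chance gives 0.889. Either way it is about 0.90, against 0.807 for the T1–T2 interaction.

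**The case against.** The best reply is that the article never states a three-level model, a 2-df interaction or an omnibus decision rule. The primary outcome, primary hypothesis and sample size fit together on a T1–T2 reading, and under that reading the named ANOVA tests the primary hypothesis exactly. Collecting ISI at T3 does not put T3 into the primary model. An objective that covers T2 and T3, followed by a primary hypothesis confined to T2, is not a contradiction. The full protocol or an analysis plan, neither of which is shown, may also specify the time levels. All of this stands, and it limits the point to a test that is not tied to its endpoint.

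Three stronger readings are tempting, and the article does not support them.

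- *The plan uses the wrong test.* A reader might infer this from the three visits. The text leaves the number of time levels open.
- *The trial has two chances at 0.05, at T2 and at T3.* With no true effect, taking whichever of T1–T2 and T1–T3 is significant would give about 9% false positives. But the primary time point is fixed as posttreatment in both the hypothesis and the outcome definition, so a claim resting on T3 would depart from the stated plan.
- *A three-level test loses power in general.* It loses power if the effect wanes partly (0.72 to 0.76 in the two cases above) and gains if the effect is fully sustained (0.845).

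The pattern with no effect at T2 and 0.8 SD at T3 shows what the three-level test can respond to. Nothing in the article suggests it is likely.

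The reply does not cover the choice of primary comparison. Keeping baseline adjustment for a post hoc step after a significant imbalance is stated in the text, not omitted from it, and it gives up precision.

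**Conclusion.** The point holds as an analysis that should be tightened. The endpoint, hypothesis and sample size all concern the T1–T2 change, and the Statistical analyses section does not tie its ANOVA to that change. If time has two levels, the test is right and N = 48 gives power 0.807. If time has three levels, the interaction would not answer the primary question: it is significant in about 84% of trials with no T2 effect and 0.8 SD at T3. Its power for a 0.8 SD T2 effect would then depend on what happens at T3, from 0.72 (halved) to 0.845 (sustained).

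Under either reading, adjusting the T2 comparison for baseline ISI raises power at the planned effect from 0.81 to about 0.90. These figures rest on an ICC of 0.54 between all visits, equal variances, complete data and, for the three-level results, assumed T3 effects.

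**What to change.** State one primary test: the between-group difference in ISI at T2, adjusted for baseline ISI, two-sided alpha 0.05, reported with its 95% CI. It can be estimated by ANCOVA or as the T2 contrast from a mixed model on the three visits. It should replace the rule that brings in ANCOVA only after a significant baseline imbalance. ANCOVA on the change score with baseline as covariate gives the same treatment effect as ANCOVA on the T2 score, so the model is already one the plan contemplates.

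Make the T3 contrast secondary, as a test of maintenance, and state that no omnibus time-by-group interaction decides efficacy.

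The cost is one or two sentences. No new data are needed and N = 48 is unchanged.

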#### Other outcome measures

Secondary outcome measures cover fatigue, anxiety and depression, subjective cognitive functioning, and societal participation. Fatigue after acquired brain injury will be assessed with the Dutch Multifactor Fatigue Scale (DMFS). The DMFS measures 5 aspects of fatigue: impact of fatigue, mental fatigue, signs and direct consequences of fatigue, physical fatigue, and coping with fatigue. All subscales of the DMFS showed sufficient to good reliability (Cronbach’s alpha = 0.70 to 0.91), good convergent validity with an existing fatigue scale, and good divergent validity with measures of mood and self-esteem [26]. Anxiety and depression symptoms will be assessed with the Dutch version of the 14-item Hospital Anxiety and Depression Scale (HADS). The reliability of the HADS is good (Cronbach’s Alpha = 0.71 to 0.90) as is the test-retest reliability (0.86–0.90) [27]. Cognitive Failure Questionnaire (CFQ) is a measure of subjective cognitive functioning. Internal consistency is good (Cronbach’s alpha = 0.88) as is the test-retest reliability (0.83) [28]. The Utrecht Scale for Evaluation of Rehabilitation—Participation (USER-Participation) is a questionnaire to rate objective and subjective participation after rehabilitation. Internal consistency is satisfactory (Cronbach’s Alpha = 0.70–0.91), and test-retest reliability is 0.65 for the frequency scale, 0.85 for the restrictions scale, and 0.84 for the satisfaction scale [29, 30].

### Other study parameters

Demographical, injury-related, and clinical variables which may influence the treatment effect will be registered: age, gender, diagnosis, time since injury, insomnia duration, use of prescribed sleep medication, use of other medication, comorbid psychiatric and somatic disorders, educational level, and currently being employed. Possible presence of sleep apnea will be screened with the Stop-Bang questionnaire [31] in participants that have not been evaluated for its presence with the gold standard overnight polysomnography [32].

### Sample size calculation

Calculation of power and group size in a repeated measures design requires an estimate of the expected intraclass correlation coefficient (ICC, within subject correlation). We therefore resorted to a recent randomized trial of Dekker and colleagues (2020) on the effect of eCBT-I on ISI in people with insomnia. We used this intraclass correlation coefficient as indication of follow-up of ISI assessments across 6 weeks in our study population with acquired brain injury. That study reported an ICC of 0.54 for ISI assessments repeated across 6 weeks in 175 people suffering from insomnia without brain injury [33]. Calculation of power and group size moreover requires an estimate of the expected treatment effect size. Whereas treatment effects of eCBT-I are often reported to be of moderate to large size, we preferred to be somewhat conservative and expect a somewhat smaller than moderate effect in the population of TBI and stroke and therefore used *f* = 0.20. Calculation of the required sample size using G*Power [34] for ANOVA, with two repeated measures and ICC of 0.54, indicated that 48 completers would provide (2 × 24), at a significance of alpha = 0.05, sufficient power (1-beta = 0.80) for a minimal detectable time-by-group interaction effect of *f* = 0.20 (small to moderate).

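### The f = 0.20 behind the 48 patients is described as small to moderate, but in the calculation used it is a 0.8 SD difference between arms, a large effect

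*Protocol article*

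**What the plan says.** In the protocol article, Sample size calculation, the authors note that "treatment effects of eCBT-I are often reported to be of moderate to large size" and then choose a lower value: "we preferred to be somewhat conservative and expect a somewhat smaller than moderate effect in the population of TBI and stroke". That is their stated reason for f = 0.20. The calculation was done "using G*Power [34] for ANOVA, with two repeated measures and ICC of 0.54", and 48 completers, 24 per arm, are said to give, at alpha 0.05, "sufficient power (1-beta = 0.80) for a minimal detectable time-by-group interaction effect" of f = 0.20. A bracket after that figure labels it small to moderate. The section gives no SD for the ISI and does not translate f into ISI points or into a standardized difference between arms.

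Under Outcomes, the primary outcome is the change in ISI at posttreatment. Under Statistical analyses, treatment effects are tested by repeated-measures ANOVA. The test that was powered is therefore the comparison of ISI change between the two arms.

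**The concern.** The usual labels for Cohen's f (0.10 small, 0.25 moderate) refer to a scale on which, for two groups, the standardized difference is d = 2f. On that scale f = 0.20 is d = 0.4, which fits the article's description. However, 24 per arm is far too few to detect a 0.4 SD difference with 80% power, even with the gain from a within-subject correlation of 0.54. Either the sample size or the description had to be on a different scale.

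At stake is what the trial can claim. A reader who trusts the paragraph will take a non-significant result as a fairly powered test that found no small-to-moderate benefit of eCBT-I. The Discussion expects the trial to help clinicians form guidelines, so that reading would matter.

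**Working it through.** **Inputs** (all from Sample size calculation): f = 0.20; m = 2 measurements; ρ = 0.54; N = 48 in k = 2 equal arms; alpha = 0.05; target power 0.80. Below, SD means the within-arm SD of the ISI at one time point, taken as equal at T1 and T2.

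**1. Reproducing the 48.** G\*Power's default for a within-between interaction uses

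λ = f² × N × m / (1 − ρ), with (k − 1)(m − 1) = 1 and (N − k)(m − 1) = 46 degrees of freedom.

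λ = 0.04 × 48 × 2 / 0.46 = 8.35, which gives power 0.807. N = 46 gives 0.790, so 48 is the smallest balanced total.

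**2. Could another option have given 48?** None of those tried does:

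| Option, f = 0.20 | N for 80% power | Power at N = 48 |
|---|---|---|
| Default, m = 2 | 48 | 0.81 |
| Default, m = 3 | 40 | 0.89 |
| Cohen (1988) effect size, m = 2 | 200 | 0.27 |
| SPSS effect size, m = 2 | 202 | 0.26 |
| Between-factor test, m = 2 | 154 | 0.34 |
| Between-factor test, m = 3 | 138 | 0.37 |

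The stated figure therefore identifies the default option. The Cohen option is the one on which f = 0.20 keeps its customary meaning of d = 0.4 in change. There λ = f² × N × (m − 1) = 0.04 × 48 = 1.92, and 200 patients would be needed.

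**3. What f = 0.20 means under the default.** Let the arms be equal at T1 and differ by D at T2, with cell means (0, 0) for TAU and (0, −D) for eCBT-I. Removing the arm and time main effects leaves an interaction effect of ±D/4 in each of the four cells. Here f is the SD of those effects divided by the within-cell SD, so

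f = D / (4 × SD), and D = 4 × 0.20 × SD = 0.80 SD.

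**4. Check by a t test on change scores.** The SD of change is SD × √(2 × (1 − 0.54)) = √0.92 SD = 0.959 SD. The standardized difference in change is 0.80 / 0.959 = 0.834. With 24 per arm the noncentrality is 0.834 × √(24/2) = 2.889, and 2.889² = 8.35, the same λ as in step 1. Power is again 0.807, and a simulation gave 0.808. The two tests are the same.

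**5. Power for other true differences, 24 per arm:**

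| Difference in change | f (default scale) | Power | Completers needed for 80% |
|---|---|---|---|
| 0.8 SD | 0.20 | 0.81 | 48 |
| 0.5 SD | 0.125 | 0.42 | 118 (59 per arm) |
| 0.4 SD | 0.10 | 0.29 | 184 (92 per arm) |

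The smallest difference detectable with exactly 80% power is 0.826 SD of change, or 0.826 × 0.959 = 0.79 SD of the ISI.

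**6. In ISI points.** The document gives no SD. On an assumed SD of 4 to 6 points, 0.8 SD is 3.2 to 4.8 points, and 0.4 SD is 1.6 to 2.4 points.

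**The case against.** The strongest reply is that nothing was miscalculated: 48 follows exactly from the stated inputs, and the sentence that 48 completers give 80% power for f = 0.20 is literally true. That stands. The fault lies in what f = 0.20 is said to represent.

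Second, the article never mentions d or SD units, so 0.4 SD is a translation and not a target the authors wrote down. That also stands, but the conclusion does not depend on it. The text says smaller than moderate. Even at 0.5 SD, the conventional moderate value, power is 0.42.

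Third, the word conservative is relative to published eCBT-I effects that the article does not quantify, so whether 0.8 SD lies below them cannot be settled from this document. This is fair as far as the literature goes. But the article describes those effects as moderate to large and places its own below moderate, and a 0.8 SD difference is not below moderate.

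Fourth, on the assumed SDs the detectable difference is below the 6-point MCID given under Outcomes, so the target may be clinically sensible. That supports keeping 48, with the caution that the MCID is worded as a reduction and not as a difference between arms. It does not support the label.

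**Conclusion.** The description of the effect size is wrong as written. The design has about 80% power for a between-arm difference in ISI change of 0.8 SD (0.83 SD of the change score), which is large on either scale. It does not have 80% power for a smaller-than-moderate effect: power is 0.42 at 0.5 SD and 0.29 at 0.4 SD, so true effects of those sizes would be missed in about 58% and 71% of such trials. These figures assume 24 completers per arm, equal variances at T1 and T2, the stated correlation of 0.54, and the default G\*Power option, which is the only one tried that returns 48. The sample size itself is not in dispute. The ISI-point equivalents rest on an assumed SD.

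**What to change.** Keep 48 and rewrite the end of the Sample size calculation along these lines:

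- State that 24 completers per arm give 80% power, at two-sided alpha 0.05 and a within-subject correlation of 0.54, for a between-arm difference in ISI change of about 0.8 SD, a large effect. Give the equivalent in ISI points with the SD used and its source.
- Name the G\*Power effect-size option.
- Remove the wording that presents the assumed effect as conservative, below moderate, or small to moderate.
- State that power is about 0.4 for a 0.5 SD difference and about 0.3 for 0.4 SD, and that a non-significant result will be interpreted from its 95% confidence interval.

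The cost is one reworded paragraph and a less favourable claim, with no extra patients. Truly powering for 0.5 SD or 0.4 SD would instead take 118 or 184 completers.

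A baseline-adjusted primary analysis would recover some precision. The residual SD would be √(1 − 0.54²) = 0.842 SD, so the detectable difference would fall to about 0.826 × 0.842 = 0.70 SD. That figure may be quoted only if the adjusted analysis is made primary. At present ANCOVA is planned only if baseline imbalance is significant.
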